#### EDA (Learning Strategies) control group

2.4.2

In order to ensure that all participants are able to potentially benefit from the study, the research team decided to deliver another intervention to those participating in the control group. This intervention will address another topic that is relevant to university students – study habits and how to improve them – but will not address alcohol and other drug use in order to not interfere with the study results.

This program is aimed at promoting the use of strategies to ease the apprehension, storage, understanding, and usability of information [35]. It is highly linked to the person's self-knowledge (strengths, weaknesses, motivation, etc); to the assigned task; and to her/his own learning process, which generally implies a high level of cognizance about the learning process [36]. EDA is delivered online in a one-on-one format. The first session includes a short introduction to the model and the administration of a five-items questionnaire to identify the dominant learning style of each participant (visual, aural, kinesthetic). During the intervention the facilitator shares a link with several activities they can work on until the next session.

#### Professional facilitators

2.4.3

The facilitators of both programs (psychologists and social workers) will have received training on each strategy. IBEM-U requires 32 h of training to be implemented. Training includes information on the risks and effects of alcohol use, the steps of the intervention, and the theoretical foundations of the intervention. Role-playing is a key component of the training. A train-the-trainer model is used to train new facilitators. The trainers for this intervention will be the developers of the original program. In the past eight years they have trained more than 150 people in Colombia, Mexico, and Brazil.

### Data analytic plan

2.5

#### Sample size

2.5.1

Sample size was determined using a simulation-based power analysis (1000 simulations), with Superpower package [37] for R, version 4.0.3 [38]. We hypothesized means for intervention and control groups for each measure with a SD of 5 and a r = 0.2 for repeated measure variables. This will mean an estimate of an effect size for group (*f* = 0.037), measurement (*f* = 0.048) and interaction between group and measurement 1-β = 0.90. The recommended *N* for each group is 191 (see). Considering the possible attrition rate of about 50%, it is planned to recruit 764 participants.

#### Random assignment

2.5.2

Randomization will take place at the level of the individual. Each participant will have a non-zero probability of being part of either the intervention or the comparison group. After filling out the baseline questionnaire, the platform generates a random number: odd numbers will correspond to the intervention group, even numbers will correspond to the control group. Research staff will inform the participant to which group they have been randomly assigned.

#### Measures

2.5.3

*Sociodemographic information* will be gathered using 12 items including contact information such as name, phone number, email, as well as age, sex, socio-economic status, hometown, living town, university school, and semester (level).

*Prevalence of alcohol use*: we will ask for lifetime, past year, past month, and past week prevalence in terms of quantity and frequency (how many standard drinks [SD] do they have and how often do they consume alcohol in those time periods).

*Binge Drinking* (BD) binge drinking will be measured by asking to male participants the number of occasions on which they have had 5 or more SD and female participants the number of occasions on which they have had 4 or more SD in the past 30 days.

*Heavy episodic drinking* (HED) will be measured by asking participants how many times they have had 10 or more SD on one occasion in the last 30 days.

*Questionnaire based on I-Change Model*: Determinants of HED will be measured via 56 items about knowledge, cognizance, risk perception, attitudes, social influence, self-efficacy, intention, and action planning. These items were adapted from the Alerta Alcohol Program from the Universidad de Sevilla and Maastricht University [39,40], and [41]. Measures for each construct are as follows:

*Knowledge* is measured by 5 items (1 = true; 0 = false) to assess knowledge about HED, including questions such as whether drinking ten or more standard drinks affects the liver, increases unwanted pregnancies, or produces neurological damage.

*Cognizance* is measured by two questions on a five-item scale (1 = completely disagree, 5 = completely agree): “I'm aware that often drink 10 or more SD per occasion,” and “I'm aware that drinking 10 or more SD per occasion affects my health.”

*Risk perception* is measured by six questions about perception of danger and seriousness on a 5-point scale (1 = completely disagree; 5 = completely agree). Examples include “Having a bad academic performance is very serious; ” “The likelihood of me having a bad academic performance are high; ” “Health problems are very serious; ”and “The likelihood of me having health problems are high.”

*Attitudes* are measured by 16 questions on a 5 -point scale (1 = completely disagree; 5 = completely agree) and assess perceived rational and emotional advantages and disadvantages of HED. Examples are: “If I drink 10 or more SD I have fun with my friends”, “If I drink 10 or more SD I fit in with other people”, “If I drink 10 or more SD I have conflicts with other people”, and “If I drink 10 or more SD I'm more vulnerable”.

*Social influence* is measured by 12 items assessing social norms, modeling, and peer pressure towards HED (1 = completely disagree; 5 = completely disagree for social norms; and 1 = Never; 5 = Always, for modeling and peer pressure). Some examples include “My loved one would approve of me drinking 10 or more SD per occasion”, “How often my loved one drinks 10 or more SD per occasion?”, and “How often I feel pressured by my loved one to drink 10 or more SD per occasion?”.

*Self-efficacy* is assessed by six items about how difficult it is (1 = very difficult; 5 = very easy) not to drink 10 or more SD per occasion in different situations such as when alcohol is offered by friends, when the person is emotionally down, or when he/she is in a family meeting.

*Intention* is measured by three items to assess the intention to drink 10 or more SD in general, the next weekend and the next month (1 = “definitely not; 5 = definitely yes).

*Action planning* is measured by eight items (1 = definitely not; 5 is definitely yes) assessing plans to not have 10 or more SD in several situations and coping plans, such as drinking drinks with low alcohol content or looking for other alternatives to be relaxed when the person feels stressed.

#### Data analyses

2.5.4

Descriptive statistics related to sociodemographic variables, alcohol use frequency and quantity, and changes in HED will be calculated. The independent variable is the participation in the IBEM-U program; dependent variables are the outcomes of the intervention in terms of alcohol use patterns and identification of factors associated with consumption (predictors = sociodemographic variables).

To determine the effect of the intervention (pre-post), we will use mixed linear models (MLM), with pre-post score, group, pre-post score*group and sociodemographics (affiliation, age, sex, program and level) as fixed effects. Participant will act as random effect, with random intercepts and random slopes for the interaction between pre-post score and group.

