### The problem of alcohol consumption

1.1

Alcohol misuse leads to several mental, physical, academic, and social problems in young adults. Among those problems, the most relevant are depression and suicidal ideation [1]; negative impacts on the immune and digestive systems, damage of the liver resulting in fibrosis or cirrhosis, as well as the link to 25 different types of cancer in the long term [[2], [3], [4]]; higher risk of unwanted pregnancies and sexual transmission infections [5,6]; a progressive decline in cognitive skills and processes of memory and planning, as well as a loss of capacity for decision-making [8,9]; National Institute on Alcohol Abuse and Alcoholism [ [10,11]. Regarding social problems, prior studies have found that high levels of drinking, especially among youth, can act as a risk factor for becoming a victim or perpetrator of violence (Pan American Health Organization [12].

Although Heavy Episodic Drinking^1^ (HED – defined as ten or more standard drinks per occasion at least once in the past month) has decreased worldwide (diminishing from 47.6% in 2000 to 43% in 2016 for current drinkers, and from 22.6% in 2000 to 18.2% in 2016 for heavy episodic drinkers), alcohol use among young adults remains a public health problem (World Health Organization [13]. The Americas region (North and Latin America) has the second highest rates of alcohol use among young adults aged between 20 and 24 years (38.2%), after the European region (43.8%) [14]. Data on excessive drinking are particularly high among university students in the Americas, pointing out that HED in the past month, corresponded to 18.6% among Latin American university students; Colombia, Uruguay, Ecuador, and Brazil have the highest levels of alcohol consumption (Organization of American States [15]. The same report states that between 60% and 87% of the Latin American university population perceived alcohol use as a severe risk to for intoxication; nevertheless, they continue excessive drinking. In Colombia, university students have the highest rates of alcohol use: 55.4% report using alcohol in the past month, compared with 38.4% of 18 to 24-year-olds and 39.7% of 25 to 34-year-olds in the general population (Comunidad Andina de Naciones [16].

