### Goals and hypotheses

2.2

The main goal of the RCT is to evaluate the effects of an adaptive program aimed at reducing frequency and quantity of alcohol use, among young adults from different universities in Colombia, compared to a control group, immediately after its implementation and six months later. The primary outcome is the number of standard drinks consumed in the past month. We hypothesize that the IBEM-U program will be effective in reducing past month alcohol consumption in undergraduate and graduate adult students, up to 15% in the experimental group. Secondary outcomes are decreasing heavy episodic drinking up to 10%. Tertiary outcomes include changes related to knowledge, awareness, risk perception, attitude, self-efficacy, intention, and action planning, regarding heavy episodic drinking.

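### The planned linear mixed model gives a valid but additive and less efficient effect for drink and heavy-episode counts, while the hypotheses are percentage reductions and no conversion is stated

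*Protocol article*

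**What the plan says.** All references are to the protocol article.

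- **Model (Data analyses).** The only effect model is given as "we will use mixed linear models (MLM"), with time (pre-post), group, their interaction and sociodemographic variables as fixed effects, and participant random intercepts and random slopes. No transformation, link function, count distribution or conversion to a percentage is given.
- **Primary outcome and hypothesis (Goals and hypotheses).** "The primary outcome is the number of standard drinks consumed in the past month". The expected reduction is "up to 15% in the experimental group".
- **Secondary hypothesis (same section).** "Secondary outcomes are decreasing heavy episodic drinking up to 10" percent, without saying whether this is relative or in percentage points.
- **Heavy episodic drinking (HED) measure (Measures).** Participants report "how many times they have had 10 or more SD on one occasion in the last 30 days", where SD means standard drinks. This is a count of occasions.
- **Background prevalence (The problem of alcohol consumption).** Among Colombian university students, "55.4% report using alcohol in the past month". Past-month HED "corresponded to 18.6% among Latin American university students".
- **Entry (Participants and recruitment).** The listed criteria set no minimum level of drinking. The Discussion expects many participants to drink little.

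**The concern.** Both outcomes are non-negative counts. Non-drinkers can enter, so many values are likely to be zero and the rest skewed. The interaction in a linear model is an absolute difference in mean change, so its size for a given percentage reduction depends on how much the sample drinks at baseline. The hypotheses are percentages.

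Two things are at stake. First, the step from the coefficient to 15% or 10% (which denominator, which interval) is left open and could be chosen after the data are seen. Second, a test of change on skewed counts loses power that a baseline-adjusted count model would recover at no cost in participants.

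**Working it through.** **1. The plan's own figure.** Sample size: 191 per group, 50% attrition. 2 × 191 / (1 − 0.5) = 764, as stated. The 191 itself cannot be rebuilt, because the hypothesised means and the interaction effect size are not printed.

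**2. Likely zeros, if the sample resembles the background populations.** Drinks: 1 − 0.554 = 44.6%. HED: 1 − 0.186 = 81.4%.

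**3. What the additive effect means as a percentage.** Inputs from Sample size: SD 5, r = 0.2, n = 191 per group, power 0.90. Two-sided alpha 0.05 is my assumption.

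Detectable difference in change = (1.960 + 1.282) × 5 × √(2 × (1 − 0.2)) × √(2/191) = 3.242 × 6.325 × 0.1023 = 2.10 drinks.

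The baseline mean is not stated. Over an assumed range, 2.10 drinks is 42% of a mean of 5, 21% of 10, 15% of 14.0 and 10.5% of 20.

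**4. Can the percentage be recovered?** Zero-heavy counts were simulated with a true 15% reduction (191 per group, 4,000 runs, 44.6% never-drinkers, assumed overdispersion). A t-test on change stood in for the interaction test.

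| Baseline mean | Mean coefficient | Coefficient / baseline | Power |
|---|---|---|---|
| 3.33 | −0.51 | −0.15 | 0.23 |
| 6.65 | −1.00 | −0.15 | 0.26 |
| 13.33 | −2.00 | −0.15 | 0.31 |

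The same percentage gives three different coefficients, but division by the baseline mean returns it.

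**5. Is the linear test valid?** With no effect, its type I error was 4.4–5.3% across drinks and HED-like counts. In separate runs on HED-like counts with 81.4% zeros (assumed mean about 0.43), the 95% interval covered 95.0–95.5% of the time.

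**6. Efficiency.** Two-wave simulations used 191 per group, 44.6% zeros, an assumed mean of 8, lognormal amounts among drinkers and a multiplicative treatment effect. The coefficient of variation (CV) among drinkers was 1.0 (overall SD about 12.5–13) or 1.5 (SD about 16–17). Power for a 30% reduction:

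| Setting | Change test | Linear, baseline-adjusted | Log-link, baseline-adjusted |
|---|---|---|---|
| CV 1.0, r about 0.61 | 0.638 | 0.790 | 0.816 |
| CV 1.5, r about 0.56 | 0.366 | 0.528 | 0.591 |
| CV 1.0, r in 0.63–0.68 | 0.69 | 0.82 | 0.85 |
| CV 1.5, r in 0.63–0.68 | 0.40 | 0.54 | 0.61 |

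A further set, comparing only the change test with the log-link model, gave 0.59 to 0.78 (CV 1.0) and 0.33 to 0.55 (CV 1.5).

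Splitting the gain in the first row: 0.790 − 0.638 = 0.152 from baseline adjustment and 0.816 − 0.790 = 0.026 from the link. In the second row: 0.528 − 0.366 = 0.162 and 0.591 − 0.528 = 0.063. Over the four rows the link adds 0.03 to 0.07.

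**7. At the hypothesised sizes.** For 15% fewer drinks, power was 0.07–0.21 (change), 0.11–0.27 (linear adjusted) and 0.14–0.29 (log-link). For 10% fewer heavy episodes, the change test had power of about 0.06.

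**8. A caution on the alternative.** For HED-like counts, the log-link test with uncorrected robust errors was itself liberal, with type I error of 7–9%.

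**The case against.** The case for leaving the model alone is substantial, and most of it stands.

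- A reader might infer that the 15% and 10% cannot be read from the linear model. They can: step 4 recovers the percentage by division. What is true is narrower, namely that the plan names no denominator or interval.
- A reader might infer that normal intervals fail with four-fifths zeros. Step 5 does not support that. Under randomisation the coefficient is an average difference in change, and it needs no normality at this size.
- A reader might say the model forces the same effect on abstainers and heavy drinkers. The random slopes in Data analyses let change vary between participants, and the fixed effect is an average.
- The zero shares are background prevalences, not forecasts for volunteers. The HED figure covers Latin America, while the article places Colombia among the countries with the highest alcohol consumption.
- The simulations assume a mean of 8, which does not fit the planned SD of 5. With 44.6% zeros and all drinkers at one value m, SD = m × √(0.554 × 0.446) = 0.497m. An SD of 5 then gives m = 10.06 and a mean of at most 0.554 × 10.06 = 5.6. A multiplicative effect also favours the log link by construction.
- The primary hypothesis is worded within one arm, and the HED target may be in percentage points. A rate ratio tests neither reading.
- A condensed article may leave derived quantities to an unseen analysis plan.

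The last objection does not remove the point. The article does not stay silent on the model: it fixes one, on a scale different from that of its hypotheses.

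**Conclusion.** The point holds as a matter of scale and efficiency, not validity. The planned analysis is additive, the hypotheses are percentages, and nothing in the article links the two. The linear test keeps its type I error at about 5%.

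Under the assumed distributions, replacing it with a baseline-adjusted log-link model raises power for a 30% reduction from about 0.33–0.64 to about 0.55–0.82 (0.40–0.69 to 0.61–0.85 in the runs with higher correlation). Baseline adjustment supplies most of that. The log link's main merit is that it estimates a ratio directly.

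Neither model rescues the stated target: at 15%, power is about 0.3 or less throughout. These figures rest on an assumed mean, dispersion and correlation, on background zero shares, and on the sole effect model applying to HED as well as to drinks. The change is worth making because it is cheap, but the planned analysis would not give a wrong answer without it.

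**What to change.** 1. **Primary analysis.** For drinks and for heavy-episode counts, use a log-link count model of the follow-up values: a negative binomial mixed model, or a Poisson GEE with small-sample-corrected robust errors. The correction matters most for HED (step 8). Include group, log(baseline + 1), a baseline-zero indicator and the planned sociodemographic covariates.
2. **Reporting.** Give the between-group rate ratio with its 95% CI. Keep the linear model as a sensitivity analysis and report its mean difference in drinks.
3. **Hypotheses.** Restate them as between-group relative reductions: a 15% reduction in drinks is a rate ratio of 0.85. State whether the 10% for HED is relative (rate ratio 0.90) or in percentage points. If the latter, a rate ratio does not test it, and a matching measure must be named.
4. **If the linear model stays primary.** Adjust it for baseline, and fix in advance the denominator and the interval method for the percentage.

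The cost is analysis wording and some programming, with no change to recruitment, measurement or the programme. The downside is that a ratio is less direct to readers than drinks per month, which is why both should be reported.

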### Study design

2.1

The effectiveness of IBEM-U to reduce problem alcohol use will be analyzed using a randomized control trial with a within-subjects design with one follow up at six months after the post-test. The intervention group will receive IBEM-U, the comparison group will receive an alternative program similar in length but focusing on learning strategies (EDA – acronym in Spanish of *Estrategias De Aprendizaje* –), aimed at promoting the use of strategies to facilitate the learning process in general. A baseline measurement (T0) will be obtained before randomization; a second measurement will occur at the end of the program (T1) – (three months after baseline); and a follow-up at six months after the second measurement (T2) (nine months after baseline).

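### The pre-post-by-group interaction is a valid test, but at the planned r = 0.2 it gives up 25% to 40% of the information that adjusting for the pre-randomisation baseline would keep

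*Protocol article*

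**What the plan says.** Section 2.5.4 (Data analyses) of the protocol article specifies "mixed linear models (MLM), with pre-post score, group, pre-post score*group and sociodemographics" as fixed effects. It adds: "Participant will act as random effect, with random intercepts and random slopes for the interaction between pre-post score and group". The listed covariates are sociodemographic only. Drinks at T0 are not among them, and nothing sets the two groups' T0 means equal.

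Section 2.5.1 (Sample size) plans "with a SD of 5 and a r = 0.2 for repeated measure variables" and attaches its power to the "interaction between group and measurement 1-β = 0.90". This gives 191 per group and, with about 50% attrition, 764 to recruit.

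Section 2.1 (Study design) states: "A baseline measurement (T0) will be obtained before randomization". T1 follows at three months and T2 at nine months after baseline.

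**The concern.** In a model with time, group and their product, where both groups have free means at T0, the product term is the difference between groups in mean change. When the correlation between occasions is low, subtracting T0 adds more noise than it removes. Randomisation after T0 makes the true T0 means equal, and an analysis that uses this fact estimates the same treatment effect with smaller variance.

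Precision is at stake. The plan expects to lose about half its participants, and the Discussion warns of high dropout, difficult recruitment and many low-level drinkers. Information that can be had from data already collected is therefore worth keeping.

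**Working it through.** **Inputs.** SD = 5, r = 0.2, 191 per group and 50% attrition come from section 2.5.1. T0 before randomisation comes from section 2.1. Assumed: equal variances at each occasion, *pre-post score* read as the time factor, and two-sided alpha of 0.05 (needed only for power).

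**The plan's own figures.** The attrition step reproduces: 191 / (1 − 0.5) = 382 per group, and 2 × 382 = 764. The 191 can be neither reproduced nor refuted, because the hypothesised means, the interaction effect size and alpha are not printed. The variance ratios below need none of these.

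**Variance factors for one follow-up, in units of SD² per participant followed up.**

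1. Participants with both measurements:
   - interaction (difference in change): 2(1 − r) = 2 × 0.8 = 1.60
   - follow-up score alone: 1.00
   - baseline-adjusted: 1 − r² = 1 − 0.04 = 0.96
   - loss: 1 − 0.96/1.60 = 40%

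2. Mixed model that also keeps T0 data from the 50% who drop out (two baselines per follow-up):
   - interaction: (1 − r²) + (1 − r)²/2 = 0.96 + 0.32 = 1.28
   - common T0 mean, or T0 as covariate: 0.96
   - loss: 1 − 0.96/1.28 = 25%

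At r = 0.2 both interaction factors exceed 1.00, so the planned contrast is less precise than one that ignores baseline. If all three occasions are modelled with a common r of 0.2 and complete data, T1 minus T0 and T2 minus T0 each have the factors in step 1.

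The sociodemographic terms do not recover the loss. They are constant within a person and enter as main effects, so they cancel from the change contrast in complete pairs.

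**Sensitivity to r.**

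| r | Complete pairs: interaction / adjusted | Loss | 50% baseline-only: interaction / adjusted | Loss |
|---|---|---|---|---|
| 0.2 | 1.60 / 0.96 | 40% | 1.28 / 0.96 | 25% |
| 0.4 | 1.20 / 0.84 | 30% | 1.02 / 0.84 | 18% |
| 0.6 | 0.80 / 0.64 | 20% | 0.72 / 0.64 | 11% |
| 0.8 | 0.40 / 0.36 | 10% | 0.38 / 0.36 | 5% |

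**Illustrative power, one follow-up, 191 followed up per group.** SE = 5 × √(2 × factor / 191), which gives 0.647 (factor 1.60), 0.579 (1.28) and 0.501 (0.96) drinks. Power is taken from the normal approximation. The differences are assumptions, since the protocol states none.

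| Assumed difference (drinks) | Interaction, complete pairs | Interaction, 50% baseline-only | Baseline-adjusted |
|---|---|---|---|
| 1.0 | 0.34 | 0.41 | 0.51 |
| 1.5 | 0.64 | 0.74 | 0.85 |
| 2.0 | 0.87 | 0.93 | 0.98 |

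**The case against.** The strongest reply is that nothing here is wrong. A time-by-group mixed model is a standard, valid analysis of a randomised trial, and sections 2.5.1 and 2.5.4 agree on the contrast. The plan reports 0.90 power for it, so no shortfall against its own target has been shown. All of this stands, and it limits the point to an efficiency gain. It does not remove the gain.

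A reader might infer several stronger things that the article does not support:

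- **A flat 40% loss.** That figure holds for complete pairs. The plan expects about 50% attrition and names a mixed model, which by default keeps baseline-only participants. The loss is then 25%.
- **A known gain in power.** No 2-drink difference appears in the article. If the printed group effect of f = 0.037 is read at face value as the SD of the group means over 5, with equal T0 means and the same difference d at T1 and T2, then (2d/3)/2/5 = 0.037 and d = 0.555. Power would be about 0.14 (interaction, complete pairs) against 0.20 (adjusted). A joint T1/T2 power, or a smaller required sample, would need further unstated assumptions.
- **Bias from chance baseline imbalance.** The change contrast is unbiased over randomisation. It subtracts any T0 difference, and at low r it over-corrects. With about 382 randomised per group, such imbalance should be modest.

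Two smaller objections have some force. The term *pre-post score* is loose. Reading it as time fits both the description of the effect as pre-post and the interaction that is powered. If baseline adjustment was meant, the text does not say so. Also, changing the primary contrast leaves section 2.5.1 describing a different one, so that section needs a matching line.

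**Conclusion.** The point holds as a free improvement and not as an error. At the plan's own r = 0.2, the interaction with free T0 means loses 25% of the information if baseline-only participants stay in the model at 50% attrition, and 40% in complete pairs. At r = 0.8 the corresponding losses are 5% and 10%. With equal variances, baseline adjustment is asymptotically never less efficient, so the recommendation does not depend on r = 0.2 being right; only its size does.

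The percentages rest on equal variances, the stated r and the reading of *pre-post score* as time. They do not depend on the effect size or alpha. The power figures depend on both and are illustrations only.

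**What to change.** In section 2.5.4, name one of these as the primary model:

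- T1 and T2 drinks as outcomes, with T0 drinks, group, time, group-by-time and the listed sociodemographics as fixed effects; or
- a constrained longitudinal model with T0, T1 and T2 as outcomes and a single T0 mean common to both groups.

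Report the group difference at follow-up as the effect. In section 2.5.1, add that 191 per group was sized on the interaction and is conservative for this contrast under the same assumptions.

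The cost is about a sentence in each section. T0 is already collected from everyone before randomisation, so no new data are needed. The covariate uses one degree of freedom, and the common T0 mean uses none.

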### Participants and recruitment

2.3

For the RCT, undergraduate or graduate students will be recruited from participant universities. Inclusion criteria include being an adult over 18 years of age, agreeing to be randomly assigned to either intervention or comparison group and being able to read Spanish. Year of school, department/university, socioeconomic status, and gender will be measured as control variables. For recruitment, 103 Colombian universities have been invited to participate, through presentations and emails. Some universities will need a formal agreement outlining the particulars of the intervention and how assessments among participants will be done; others will extend the invitation to students for them to participate by themselves. Multiple strategies will be used to recruit participants; they will include a call for participation sent by the universities, through social media, institutional emails, and promotional videos. Invitations will include the link for registration, where we will ask for name, email, and phone number. The information will be hosted in the [Corporación Nuevos Rumbos] server with only the research team having access. The researchers will contact the registered participants and give detailed information about the procedure and send informed consent forms for participation, inviting them to accept or refuse the intervention. The consent form specifies that the collected information will be confidential, that it will be used for the intervention and research goals, and that they will be randomly assigned to either IBEM-U or EDA. Individuals participating in other alcohol prevention program will be excluded. As the intervention is online, contamination is considered unlikely. Those students who agree to participate will receive a link to fill out the measurement instruments and schedule an appointment for the first meeting on one of the two programs.

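### Socioeconomic status is declared a control variable and collected, but the only effect model leaves it out; this is minor, and matters mainly through the expected attrition

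*Protocol article*

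**What the plan says.** Three places in the protocol article bear on the adjustment variables.

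- Section 2.3 (Participants and recruitment): "Year of school, department/university, socioeconomic status, and gender will be measured as control variables".
- Section 2.5.3 (Measures), on the sociodemographic items, which after contact details include: "as well as age, sex, socio-economic status, hometown, living town, university school, and semester (level").
- Section 2.5.4 (Data analyses), on the effect model: "we will use mixed linear models (MLM), with pre-post score, group, pre-post score*group" and "sociodemographics (affiliation, age, sex, program and level) as fixed effects". The random part follows: "Participant will act as random effect, with random intercepts and random slopes for the interaction between pre-post score and group".

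Section 2.5.4 also states a second purpose: "identification of factors associated with consumption (predictors = sociodemographic variables").

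On outcome and size: "The primary outcome is the number of standard drinks consumed in the past month" (2.2). The sample size in 2.5.1 was simulated "with a SD of 5 and a r = 0.2 for repeated measure variables", giving 191 per group and, with about 50% attrition, a recruitment target of 764.

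**The concern.** A variable called a control variable has a function only if some analysis controls for it. The article writes down one effect model, and its bracketed list of sociodemographics reads as complete. SES is not on it. SES is collected, so lack of data does not explain the gap.

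Two things are at stake. First, the treatment estimate: about half the participants may have no later measurement. If those who stay differ in SES between the arms, a model without SES compares unlike groups at post-test. Second, the search for sociodemographic factors associated with consumption: if it is read from the same model, no SES association can be reported, and coefficients of variables correlated with SES absorb part of it.

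**Working it through.** **1. The lists side by side**

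| Item | 2.3 control variable | 2.5.3 collected | 2.5.4 in model |
|---|---|---|---|
| Year of school / semester / level | yes | yes | yes |
| Department, university / program, affiliation | yes | yes | yes |
| Gender / sex | yes | yes | yes |
| Socioeconomic status | yes | yes | **no** |
| Age | not named | yes | yes |

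Matching names generously, SES is the only declared control variable missing from the model.

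**2. The plan's own figure**

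2 × 191 / (1 − 0.5) = 764, which agrees with 2.5.1. The 191 itself cannot be rebuilt, because the hypothesised means are not in the text at hand. No sample-size figure depends on this point.

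**3. Complete data**

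Inputs: σ = 5 and ρ = 0.2 (2.5.1), 191 per arm. I take σ to be in the units of the primary outcome. The sociodemographics enter as time-constant main effects. An SES effect that is the same before and after cancels from each participant's change, so the pre-post by group estimate is the same with or without SES. Its standard error is √[2 × 2(1 − ρ)σ²/n] = √(80/191) = 0.647.

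A simulation of 60 trials, fitting age and sex in one model and SES and sex in the other, gave estimates that differed by about 10⁻¹⁴, with a mean SE of 0.650 in both.

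**4. About 50% attrition**

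Take n = 382 randomised and m = 191 with a post-test per arm. A mixed model using all available scores has variance per arm

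σ²[(1 − ρ²)/m + (1 − ρ)²/n] = 25 × [0.96/191 + 0.64/382] = 0.1675,

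so SE = √(2 × 0.1675) = 0.579.

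Let R² be the share of outcome variance explained by SES (assumed 0.01 to 0.10). Let Δ be the between-arm difference in (mean SES of those who stay minus mean SES of all randomised), in SES standard deviations. Baseline scores correct only a fraction ρ of the gap, so leaving SES out moves the estimate by approximately

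(1 − ρ) × σ√R² × Δ = 4√R² × Δ.

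*(a) Dropout unrelated to SES, or related equally in both arms.* Δ averages zero. Taking dropout as unrelated to SES, its SD is √[2(1/191 − 1/382)] = 0.0724, so its mean absolute size is 0.798 × 0.0724 = 0.0577.

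- R² = 0.01: 4 × 0.1 × 0.0577 = 0.0231, or 0.0231/0.579 = 0.04 SE.
- R² = 0.10: 4 × 0.316 × 0.0577 = 0.073, or 0.13 SE.

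Simulation gives about 0.04 to 0.12 SE. A separate simulation had dropout equally SES-related in both arms, SES and age both prognostic, and the age model set against the SES model. The estimates differed by 0.06 on average and 0.22 at most against an SE of about 0.57, that is 0.1 SE and under 0.4 SE.

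*(b) SES-related dropout that differs by arm.* Δ no longer averages zero, so the shift is a bias. For illustration take Δ = 1/3.

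- R² = 0.01: 4 × 0.1 × 0.333 = 0.133, or 0.23 SE.
- R² = 0.10: 4 × 0.316 × 0.333 = 0.422, or 0.73 SE.

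This agrees with a simulated range of roughly 0.2 to 0.75 SE, which adding SES to the model essentially removes. The bias is proportional to Δ, so a stronger difference between arms would give more.

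For scale, the interaction detectable with 90% power at 191 complete pairs per arm is (1.96 + 1.28) × 0.647 = 2.10. A bias of 0.13 to 0.42 is about 6% to 20% of that.

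**5. The second aim**

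Here the covariate coefficients are themselves results, so the cancellation in step 3 gives no protection. SES is grouped with the sociodemographic items in 2.5.3, yet the only model written cannot estimate its association with drinking.

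**The case against.** The strongest reply is that 2.3 sits in the recruitment section and says only that the variables will be measured, while 2.5.4 is the analysis section and governs. On that reading one model is specified and should be followed. This is right as far as it goes. A reader might infer that the trial has two competing adjusted primary estimates, but 2.3 names no model, outcome or estimate, and an analysis using its list in place of the 2.5.4 list would depart from the stated model. What remains is that 2.3 assigns SES a role that 2.5.4 does not carry out.

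A reader might also infer that a chance SES imbalance stays in the estimate, or that free choice between covariate sets raises the 5% error rate to some 5.5–6.5%. Both ideas belong to a post-only or group main-effect comparison. The written model has a pre-post by group term, and with complete data that estimate is the same under either set, so there is neither a shift nor any error inflation. Chance imbalance under randomisation is in any case not bias.

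Age is not a second contradiction: 2.3 does not claim to be exhaustive. Nor is gender against sex shown to cause any error.

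Finally, the article is condensed and a fuller analysis plan may hold the definitive list. That may settle the matter elsewhere, but the article states both lists itself and they do not agree on SES.

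**Conclusion.** The inconsistency is real and minor. SES is declared a control variable and collected, and the only effect model omits it. With complete data the consequence for the pre-post by group estimate is zero. With attrition of about 50% it is about 0.04–0.12 SE if dropout is unrelated to SES or equally related in both arms, and a bias of roughly 0.2–0.75 SE if SES-related dropout differs by arm.

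These sizes rest on assumptions: SES explaining 1–10% of outcome variance with the same effect before and after; all the attrition falling at the post-test; σ = 5 and ρ = 0.2 as in 2.5.1; and, for the larger range, completers whose mean SES differs between arms by about a third of a standard deviation. The article predicts high dropout but does not say who will drop out, so the differential case is a possibility and not a forecast. Its direction is unknown. The effect on the second aim does not depend on attrition.

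**What to change.** Add socioeconomic status to the sociodemographic fixed effects in 2.5.4, and give that same list in 2.3. State that the set is used in the effect model whatever the observed balance between arms.

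The change is wording in two sentences. SES is already collected at baseline, and the target of 764 is unaffected. The cost is a few degrees of freedom: one if SES enters as a score, or the number of categories minus one if it enters as a factor. The protection it gives against SES-related dropout holds if the SES effect is stable over time and if dropout depends only on SES, the other covariates and the observed scores.

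If SES is meant to stay out of the model, the alternative is to drop it from the control variables in 2.3. That removes the contradiction but gives up the protection and the SES result for the second aim.
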